## Abstract

**Background:**

Spontaneous recovery from articular cartilage injury is difficult, and the ongoing progression of disease can eventually lead to osteoarthritis. Currently, there is no effective non-surgical treatment for articular cartilage injury. Arthroscopic debridement and microfracture surgery are performed for fibrocartilage repair. But fibrocartilage is different from normal articular cartilage, and functional recovery is not satisfactory. Therefore, it is necessary to develop more effective techniques for articular cartilage repair. Progress in material science, cell biology, biomechanics, and bioreactor technology has allowed the development of biomimetic, tissue-engineered osteochondral composites that have shown potential for the repair of damaged cartilage. We prepared biomimetic, tissue-engineered cartilage scaffolds optimized for biochemical composition and structural characteristics. Based on the experience of our pre-clinical studies on animals, a human articular cartilage acellular matrix scaffold was prepared and is in clinical use. The combination of autologous chondrocytes and scaffolds has shown satisfactory results in repairing cartilage defects in preliminary experiments.

**Methods:**

This is a prospective randomized controlled trial. One hundred patients with full-thickness cartilage injury of the knee will be randomly divided into two groups to receive treatment with either tissue-engineered cartilage constructed using biomimetic cartilage extracellular-matrix-oriented scaffolds combined with autologous chondrocytes, or arthroscopic debridement and microfracture surgery. There will be five visiting time points: at baseline, then at 3, 6, 12, and 18 months postoperatively. The primary outcome will be therapeutic efficacy as assessed by the Lysholm score at 12 months postoperatively. The secondary outcomes will be the International Knee Documentation Committee score, Visual Analog Scale score, and cartilage injury and repair as assessed by magnetic resonance imaging as well as the incidence of postoperative adverse events.

**Discussion:**

This trial will attempt to verify the use of tissue-engineered cartilage constructed using autologous chondrocytes combined with allogeneic, acellular cartilage matrix for the repair of cartilage defects, thereby providing favorable evidence for its use in clinical practice.

**Trial registration:**

ClinicalTrials.gov, identifier: NCT02770209. Registered on 11 May 2016.

**Electronic supplementary material:**

The online version of this article (doi:10.1186/s13063-017-2251-6) contains supplementary material, which is available to authorized users.

## Background

Injured articular cartilage has limited capacity for self repair. Without timely, early, and effective treatment, damage to the articular cartilage progressively worsens, resulting in joint swelling, pain, and dysfunction. The patient ultimately develops osteoarthritis and may require artificial joint replacement. Clinical therapy for cartilage damage includes microfracture surgery and autologous osteochondral transplantation. However, the microfracture technique is limited to small-scale damage, and autologous osteochondral transplantation is hindered by limited supply. With advances in material science, cell biology, biomechanics, and bioreactor technology, the new generation of biomimetic, tissue-engineered osteochondral composites display great potential for the repair of cartilage damage [1, 2].

Currently, in cartilage tissue engineering, seed cells are derived from autologous or allogeneic chondrocytes, mesenchymal stem cells, embryonic stem cells, or pluripotent stem cells [3, 4]. Increasing evidence indicates that bone marrow mesenchymal stem cells can be induced to differentiate into chondrocytes, and these cells have been successfully used in the treatment of large-size bone defects, cartilage lesions, and spinal cord injury [5, 6]. The quality and quantity of bone mesenchymal stem cells gradually decreases with age, especially in patients with degenerative diseases [7]. Adipose stem cells and umbilical cord mesenchymal stem cells are abundant and have similar characteristics to bone mesenchymal stem cells, and both of these cell types can be induced to differentiate into chondrocytes [8, 9]. Adipose stem cells and umbilical cord mesenchymal stem cells have been used to repair cartilage defects, but the findings are still preliminary, and these cells cannot be harvested or cultured in large quantities. Furthermore, the use of embryonic stem cells is complicated by ethical considerations. As a consequence, autologous chondrocytes are optimal seed cells for cartilage tissue engineering [10].

The transplantation of autologous chondrocytes in combination with tissue-engineered cartilage scaffolds to repair cartilage damage requires researchers to focus on two major issues, namely (1) the in vitro amplification of chondrocytes and (2) the preparation of biocompatible chondrocyte scaffolds [11]. The preparation of chondrocyte scaffolds requires advanced technique, and currently, only the Institute of Orthopedics at the Chinese PLA General Hospital has the capacity to produce acellular cartilage; there is no other source of tissue-engineered cartilage scaffolds in China.

### Preliminary experiments

A proprietary allogeneic, acellular, cartilage-oriented scaffold was successfully created by the Cartilage Tissue Engineering Research Group, Institute of Orthopedics, Chinese PLA General Hospital (with intellectual property rights). The innovative scaffold simulates the composition and spatial structural characteristics of normal cartilage. The preparation methods are as follows: articular cartilage is pulverized to obtain natural cartilage extracellular matrix, which is identical in biochemical composition to extracellular matrix of natural articular cartilage. Then, a porous sponge-like scaffold is prepared using a freeze-drying technique [12]. In vitro experiments and large-animal, articular cartilage injury repair experiments have produced good results [13–15]. Using this material, our research group prepared biomimetic cartilage tissue-engineered scaffolds, which mimic the structural characteristics of natural articular cartilage extracellular matrix. This allogeneic, acellular cartilage scaffold has the following characteristics: (1) it is derived from allogeneic cartilage, and the extracellular matrix remains intact after allografting, helping to maintain the numerous components of normal cartilage, particularly type II collagen and proteoglycans, resulting in enhanced repair. Cartilage scaffolds used outside of China are mainly composed of types I and III collagen or hyaluronic acid, and vary greatly from natural cartilage components [16]. The original cartilage structure is difficult to reproduce with these types of scaffolds, and fibrous cartilage may affect treatment outcome; (2) the biomimetic scaffold has a similar three-dimensional structure to that of normal articular cartilage, which is the oriented scaffold structure. The scaffold imitates the orientation of normal cartilage cells, which are arranged perpendicular to the surface, and provides a paratactic columnar structure that contributes to the columnar arrangement of cells (Fig. 1) [15]. This structure in combination with type II collagen and proteoglycans derived from normal articular cartilage results in a scaffold structure that is extremely close to that of normal joint cartilage. Consequently, the repaired cartilage will have normal structure and function; (3) the oriented scaffold has a good biomechanical property. Its compressive stress is better than the non-oriented scaffold in wet and dry conditions (Fig. 2); and (4) the oriented scaffold has good biocompatibility. Preliminary experiments have investigated the immune responses of the oriented scaffold of heterogeneous (porcine) and conspecific (rabbit) acellular cartilage. After the oriented scaffold had been implanted into the rabbit, its immune responses were observed from the aspects of cellular immunity and humoral immunity. Results suggested that its immunogenicity was low. Thus, it is verified that the oriented scaffold of acellular cartilage has good biocompatibility [17].

**Fig. 1 Fig1:**
[figure not shown]
Allogeneic, acellular cartilage scaffolds. Scaffold pores exhibit a parallel arrangement, which is conducive to the growth of cells along the pores. Cells are arranged in a column during proliferation. Cells display a columnar arrangement in line with the normal structural arrangement of articular cartilage, which is conducive to the formation of normal articular cartilage. The pore structure of the oriented scaffold also allows the metabolism of cell nutrition. **a** Light microscope × 100. **b** Scanning electron microscope × 100

**Fig. 2 Fig2:**
[figure not shown]
Compressive stress-strain curves. Comparison of biomechanical properties of oriented and non-oriented scaffolds of allogenic, acellular cartilage. **a** Comparison of compressive stress between the oriented and non-oriented scaffolds in a wet condition. **b** Comparison of compressive stress between the oriented and non-oriented scaffolds in a dry condition

### Theoretical evidence

Cartilage has limited regenerative capacity and can only be repaired using autologous, allogeneic cartilage or artificial substitute materials after injury. However, these repair methods have limited effectiveness. Autologous chondrocyte transplantation may have significant side effects, while allogeneic cartilage or artificial substitute materials have poor biocompatibility. Tissue-engineered cartilage may provide an alternative means of repairing damaged cartilage. After autologous chondrocytes cultured in vitro are combined with a biomimetic cartilage scaffold, the tissue-engineered cartilage is constructed in vitro and transplanted into the site of injury to repair the cartilage. This strategy may restore articular cartilage function, providing a novel method for the treatment of cartilage defects.

### Reason for establishing a control group

Microfracture is an arthroscopic bone marrow stimulation technique first applied in clinical practice by Steadman and Rodrigo in 1985. During microfracture surgery, damaged articular cartilage is cleaned until the edge of the normal articular cartilage and subchondral bone marrow cells, chondrocytes, and bone cells penetrate into the damaged area through a hole made using an awl on the surface of the exposed subchondral bone. Blood clots seeping out of the hole adhere to surrounding normal cartilage tissues forming a fibrous cartilage repair defect area responsible for joint function recovery [18]. Arthroscopic microfracture is the most widely used method for the surgical repair of articular cartilage injuries because it is a simple operation with satisfactory clinical efficacy [19]. Here, microfracture surgery will be used as a control for the repair of articular cartilage injury.

## Methods/design

### Study objectives

We hypothesized that autologous-cell-derived, tissue-engineered cartilage is superior to microfractures in the treatment of knee cartilage injury.

The main objective of the study is to evaluate the functional and symptomatic recovery in patients with knee joint cartilage injury undergoing autologous-cell-derived cartilage treatment and to compare it with microfracture surgery, based on Lysholm scores at 12 months postoperatively as the primary outcome measure.

The secondary objective of the study is to (1) compare the effectiveness of the two repair methods on knee function recovery based on International Knee Documentation Committee (IKDC) scores, (2) compare the effectiveness of the two repair methods on pain relief, (3) assess cartilage regeneration by magnetic resonance imaging (MRI), and (4) compare the safety of the two repair methods for knee cartilage repair.

### Study design

This prospective, single-blind, randomized controlled clinical trial will be conducted at the Institute of Orthopaedics, Chinese PLA General Hospital, China. The study design is compliant with the Standard Protocol Items: Recommendations for Interventional Trials (SPIRIT) Statement [20] (see Additional file 1). After providing informed consent, the potential patients with full-thickness cartilage injury of the knee joint will be screened according to the inclusion and exclusion criteria, and finally, 100 eligible patients will be randomly assigned to receive autologous-cell-derived tissue-engineered cartilage grafts (*n* = 50) or microfractures (*n* = 50). The primary outcome is therapeutic efficacy as assessed by the Lysholm score at 12 months postoperatively. The secondary outcomes are the IKDC score, Visual Analog Scale (VAS) score, and cartilage injury and repair as assessed by MRI as well as the incidence of postoperative adverse events (see the trial flow chart in Fig. 3). The Standard Protocol Items: Recommendations for Interventional Trials (SPIRIT) Figure is detailed in Fig. 4.

**Fig. 3 Fig3:**
[figure not shown]
Flow chart of the trial

**Fig. 4 Fig4:**
[figure not shown]
Standard Protocol Items: Recommendations for Interventional Trials (SPIRIT) Figure

### Inclusion criteria

Patients meeting all of the following criteria will be considered for admission to the trial:○ Patients with full-thickness cartilage injury of the knee joints○ Patients with normal joint movement and a stable joint (without injury or less than one third excision of the meniscus; normal cruciate ligament, lateral and medial collateral accessory ligament, or normal Q-angle and patellofemoral joint trajectory after transplantation, or corrected to normal by surgery), and without valgus or varus deformity○ Patients aged 18–50 years of age (patients over 50 years of age have poor viability of autologous chondrocytes)○ Patients with focal cartilage defects diagnosed by arthroscopy, Outerbridge III/IV grade, cartilage defect size 1–5 cm^2^, intact articular surface (lower than grade II injury according to the Outerbridge classification), and one or two lesions in the same joint○ Patients and their families who are informed of the treatment and who provide signed informed consent

### Exclusion criteria

Patients presenting with one of the following criteria will not be included in the trial:○ Autoimmune disease (rheumatoid arthritis, chronic kidney disease)○ Hematonosis (thrombocytopenia, leukemia)○ Topical steroid therapy within 3 months○ Bleeding tendency○ Drug addiction (including narcotic, anesthetic, or alcohol addiction)○ Inflammatory joint disease (specific or non-specific arthritis)○ Contagious viral infection○ Metabolic diseases (gout or rheumatism)○ Body Mass Index > 30 kg/m^2^
○ Pregnant or lactating women, or planning to become pregnant within 1 year after initial registration○ Psychological mental illness, cannot cope with rehabilitation

### Recruitment

Patients with full-thickness cartilage injury of the knee joint will be recruited from outpatients and inpatients at the PLA General Hospital. Patients who are interested in participation in the trial can contact the sponsor through their attending physicians via telephone, Email, or WeChat. Recruitment information will be issued through hospital websites, social software, and posters.

### Randomization and blinding

A randomization sequence table will be generated using SAS 9.1 software (copyright SAS Institute Inc., Cary, NC, USA) by professional statisticians who will not participate in the trial. Each patient will be randomly assigned a sequence number. The random number will be concealed in sealed envelopes and saved by a researcher who will not participate in the trial. If severe adverse events occur, the researcher will be informed of the need to open the envelope through communication from the principal investigator in situations where code break is warranted. After providing informed consent, eligible patients will be assigned randomly. The final unblinding will be done after data collection.

Surgeons and patients will be aware of the surgical methods used, and evaluators and statisticians will be blinded to group information.

### Interventions

#### Therapeutic approach

##### Interventions in the experimental group

Patients in the experimental group will be treated with the biomimetic cartilage matrix combined with autologous chondrocytes. The entire course of treatment includes two surgeries. The first surgery will be performed to observe articular cartilage damage by arthroscopy and assess treatment potential. If the patient’s condition meets the surgical requirement, we will extract cartilage from the intercondylar fossa non-weight-bearing area during the first surgery. Chondrocytes will be in vitro-amplified and inoculated into the cartilage scaffold at a density of about 1 × 10^7^/mL. The fully prepared seeded scaffold will be implanted into the site of injury during the second surgery.

First surgery (arthroscopic assessment of cartilage damage and harvesting of cartilage seed cells): the scope, location, and size of articular cartilage injury will be assessed with preoperative MRI. Joint ligament and meniscus injury will be evaluated. Mechanical distribution of bony structure around the joint will be evaluated with X-ray examination. Anesthesia will include regional block, spinal anesthesia, or general anesthesia. Patients will be restrained in the supine position during arthroscopy, with their limbs lowered, followed by arthroscopic debridement of the knee joint (including joint lavage, synovectomy, treatment of articular cartilage damage, removal of loose bodies and osteophytes, meniscus surgery, intercondylar fossa and anterior cruciate ligament impingement syndrome treatment).

Assessment and sampling: articular cartilage damage, including the severity, location, size, and depth, will be assessed by arthroscopy. Normal, full-thickness cartilage 100-200 mg (approximately 0.5 cm × 1 cm) will be harvested from the non-weight-bearing area of the femoral condyle or the intercondylar fossa.

Obtaining chondrocytes: the harvested cartilage tissue will be preserved and transported in a 50-mL centrifuge tube containing 8 mL of tissue preservation solution, placed on a test tube rack on top of an ice pack, at 4 °C under sterile conditions. Cartilage tissue will be transferred to the Institute of Orthopedics at the Chinese PLA General Hospital within 12 h. In strict accordance with the requirements and inspection standards of the National Institutes for Food and Drug Control, autologous chondrocytes will be isolated, cultured, expanded, and quality controlled. The culture period will be 3–4 weeks. The cultured cells will be tested for cell viability and secretory function, as well as for bacterial and mycoplasma contamination. Experimental data will be recorded, and figures will be generated. Obtained cartilage seed cells will be frozen in liquid nitrogen for the construction of autologous-cell-derived tissue-engineered cartilage.

Construction of the in vitro tissue-engineered cartilage: after cell culture and expansion, the collected cell suspension will be transferred to a centrifuge tube and centrifuged at 1000 rpm for 10 min to obtain a cell pellet. The supernatant is discarded. The cell pellet will be placed into 10 mL of culture medium, pipetted evenly, and then centrifuged for 10 min and the supernatant discarded. Then, 1 mL of the culture medium will be added to resuspend the chondrocytes followed by inoculation onto a biomimetic cartilage scaffold, forming a bionic cartilage patch. The patch is incubated in an incubator for 30 min before use in surgery.

Second surgery (autologous chondrocyte-constructed, tissue-engineered cartilage for the repair of articular cartilage damage): tissue-engineered cartilage constructed using autologous chondrocytes will be implanted to repair the damaged articular cartilage. Rehabilitation therapy will follow after repair surgery.

Construction of tissue-engineered cartilage in vitro: human chondrocytes will be stored in cryotubes in liquid nitrogen. The cells will be placed in warm water at 40 °C to thaw them within 1 min. The cells will then be transferred into a centrifuge tube and centrifuged for 10 min at 1000 rpm and the supernatant will be discarded. Cells will be resuspended in a 10-mL volume of culture medium, triturated and centrifuged for another 10 min, and the supernatant will be discarded. The cells will be resuspended in fresh culture medium and incubated at 37 °C under 5% CO_2_. Subsequently, the chondrocytes will be seeded onto biomimetic cartilage matrix scaffold to prepare tissue-engineered cartilage.

Eligibility criteria for surgeons: (1) attending physicians with more than 10 years of standing and experience, (2) experience of more than 200 arthroscopic surgeries per year, and (3) having experience and ability to deal with emergencies. Cell culture and construction of tissue-engineered cartilage will be done by a specially trained technologist-in-charge.

##### Interventions in the control group

Patients in the control group will be subjected to arthroscopic debridement and microfracture surgery. Regional block, intraspinal anesthesia, or general anesthesia will be used during surgery. Patients will be restrained in a supine position during arthroscopy, with their affected limb drooped, followed by joint debridement, including joint lavage, synovectomy, treatment of articular cartilage injury, removal of free bodies and osteophytes, meniscus surgery, treatment of intercondylar fossa and anterior cruciate ligament impingement syndrome. After removal of floating cartilage pieces, the joint will be cleaned of calcified bone using a scraper, and tiny fracture holes will be drilled outwardly in a rotational manner with an interval of 3–4 mm at the center of the subchondral bone to ensure the leakage of blood and bone marrow (containing some stem cells) from the holes to form blood clots that differentiate into chondrocytes. After surgery, these chondrocytes will gradually become fibrous cartilage components.

Eligibility criteria for surgeons: (1) attending physicians with more than 10 years of standing and rich experience, (2) experience of more than 200 arthroscopic surgeries per year, and (3) having experience and ability to deal with emergencies.

#### Concomitant care and interventions

Proper rehabilitation and good lifestyle will allow patients to regain their health as soon as possible. The following actions should be avoided to obtain maximum rehabilitation including: sitting on a low bench (about 20 cm in height), using a squat-toilet, strenuous exercise, accidental falls, internal and external rotation of the knee joint, and lying on the affected side. After muscle-strength training, patients will feel mild muscle soreness. The presence of mild muscle soreness and ligament strain or muscle soreness at the second day after exercise is normal and will lead to strengthened muscles and stabilized joints. However, a rest plus ice compress is necessary if the pain lasts for several days, which indicates excessive exercise. If the knee pain is severe and the patient’s activities are severely limited, patients should see a physician immediately.

### MRI determination

#### In vivo evaluation of regenerative cartilage with T2 value

The T2 value is sensitive to the orientation and concentration of collagen, the integrity of the collagen network and water content in cartilage (Fig. 5). To longitudinally evaluate the water content and collagen fiber orientation of cartilage with T2 mapping, MRI examination of T2 mapping will be performed and T2 values of regenerative cartilage will be measured at 3, 6, 12, and 18 months post operation.

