**Fig. 5 Fig5:**
[figure not shown]
Example of the measurement of T2 values. The regenerative cartilage in this case is located in the medial femoral condyle. **a** Shows the T2 value of regenerative cartilage. **b** Shows the T2 value of normal control cartilage. The color in the region of interest indicates the T2 value

T2 mapping is a functional index to evaluate the composition of articular cartilage. The spatial distribution of T2 indicates the water and collagen content and improvement of the direction, which is beneficial for the objective and dynamic monitoring of the regenerated cartilage. The T2 value of the cartilage is an important indicator to measure the structural integrity of collagen fibers, based on which, we can dynamically detect the biochemical properties and maturation process of the repaired tissues.

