#### In vivo evaluation of regenerative cartilage with △R1 value

Delayed Gadolinium-enhanced Magnetic Resonance Imaging of Cartilage (dGEMRIC) is an imaging technique that indirectly reflects joint cartilage glycosaminoglycan (GAG) content based on the ion distribution of fixed charge density (FCD) (Fig. 6). GAG molecules with negatively charged hydroxyl and sulfate groups indicate cartilage FCD. Gd-DTPA^2−^, an MRI contrast agent, is also negatively charged, and its distribution in the cartilage is negatively correlated with FCD; therefore, there is a negative correlation between Gd-DTPA^2−^ distribution and GAG content. △*R1* = 1/*T1*post−1/*T1*pre. Higher GAG content is accompanied by gradually reduced △*R1* values, which is used to determine regeneration of the regenerated cartilage [21].

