### Statistical analysis

Data will be analyzed using SPSS19.0 software (IBM Corp., Armonk, NY, USA). A statistical significance level of 0.05 will be used. Normally distributed data will be expressed as the mean ± standard deviation, and non-normally distributed data will be expressed as the median, minimum, and maximum. Classified variables will be expressed as a number and percentage.

The analysis will be performed on the basis of the intent-to-treat principle. A full analysis set following the principle of intent-to-treat will consist of a data set for all patients who participated in the trial, regardless of compliance or withdrawal. For patients who are lost to follow-up, the missing data will be imputed by the last-observation-carried-forward method based on the final observed value.

Descriptive statistics will be used for baseline feature data. Pearson’s chi-squared test or Fisher’s exact test will be used for intergroup comparisons of categorical variables, such as curative outcomes and postoperative incidence of adverse events. For independent variables, such as IKDC score, VAS score, T2 value, and △*R1*, an independent sample *t* test or the Mann-Whitney *U* test will be used.

A multivariate logistic regression analysis model will be used to adjust for possible confounding variables such as age, sex, etiology, cartilage defect area, meniscus injury, course of disease, severity of cartilage injury, postoperative complications, and surgeon (experience).

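### T2 and ΔR1 are defined only where repair tissue exists, so these two MRI measures compare tissue quality given formation and cannot show whether tissue formed

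*Protocol article*

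**What the plan says.** Under Study objectives, one secondary aim is to "assess cartilage regeneration by magnetic resonance imaging (MRI"). The Secondary outcome measures section lists MRI evaluation of repair and regeneration at baseline and at four post-operative visits, without naming a variable there.

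The MRI determination section describes two measures:

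- **T2:** "T2 values of regenerative cartilage will be measured at 3, 6, 12, and 18 months post operation". The text with Fig. 5 explains that "T2 mapping is a functional index to evaluate the composition of articular cartilage", and the caption says that the example panel "Shows the T2 value of regenerative cartilage".
- **ΔR1:** it reflects glycosaminoglycan content, "which is used to determine regeneration of the regenerated cartilage".

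Statistical analysis gives the continuous variables as "such as IKDC score, VAS score, T2 value, and" ΔR1, to be compared by a t "test or the Mann-Whitney" U test. The same section sets an intent-to-treat full analysis set, and last observation carried forward for patients lost to follow-up. It names Pearson's chi-squared or Fisher's exact test for categorical outcomes.

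**The concern.** The objective is regeneration, but both named measures are properties of tissue that has already regenerated. A microfractured defect that did not fill, or a graft that was lost, offers nothing on which to measure them.

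The stated rules do not supply a value:

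- Intent-to-treat keeps the patient in the set but creates no T2.
- Carrying forward is written for loss to follow-up, and this patient has attended.
- T2 of repair tissue begins at 3 months, so a knee that never formed tissue has no earlier value. Where tissue formed and was later lost, an earlier value would describe tissue that is no longer there.

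The test then runs on knees selected by a post-randomisation treatment result. If the arms differ in how often repair fails, the arm with more failures loses its worst knees and the comparison is no longer between randomised groups.

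**Working it through.** The article gives no T2 or ΔR1 effect, no standard deviation and no rate of absent tissue, so there is no planned figure to reproduce. What follows is an illustration on stated assumptions.

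**Inputs.** From Sample size: efficacy 78% (microfracture) and 97% (graft), 50 per arm, two-sided 0.05. Under the definition in Primary outcome measure, failure means a Lysholm score of 0–59, so the failure rates are 100 − 78 = 22% and 100 − 97 = 3%. *Assumption:* 25%, 50% or 100% of these rates is the share with no measurable tissue. Nothing in the article links the two.

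**Model.** Latent repair quality is N(0,1) in control and N(d,1) in graft. Knees below a common cut-off have no measurable tissue. Let p be the share absent, z = Φ⁻¹(1 − p) and λ = φ(z)/(1 − p).

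- True difference: d = z_graft − z_control
- Difference among measurable knees: d + λ_graft − λ_control
- SD within an arm after truncation: √(1 − zλ − λ²)
- Standardised difference: the observed difference divided by the root mean of the two variances

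| Share of Lysholm failure rates | 25% | 50% | 100% |
|---|---|---|---|
| Absent, control / graft | 5.5% / 0.75% | 11% / 1.5% | 22% / 3% |
| Absent knees of 100 (control) | 3.1 (2.75) | 6.25 (5.5) | 12.5 (11) |
| z, control / graft | 1.598 / 2.432 | 1.227 / 2.170 | 0.772 / 1.881 |
| True d | 0.83 | 0.94 | 1.11 |
| λ, control / graft | 0.118 / 0.021 | 0.211 / 0.038 | 0.380 / 0.070 |
| Observed raw difference | 0.74 | 0.77 | 0.80 |
| SD, control / graft | 0.893 / 0.974 | 0.834 / 0.957 | 0.750 / 0.929 |
| Standardised difference | 0.79 | 0.86 | 0.95 |
| Loss, raw | 12% | 18% | 28% |
| Loss, standardised | 5% | 9% | 15% |

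Truncation also narrows the spread within each arm, so the standardised loss is the one that bears on the test. In this model the t test on measurable knees still has about 97% to 99% power at 50 per arm.

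**Only formation differs, composition identical.** Rejection rates at 50 per arm, with the same absence rates:

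| Analysis | 25% | 50% | 100% |
|---|---|---|---|
| t test on measurable knees (simulated) | 5% | 5% | 5% |
| Mann-Whitney, no tissue ranked worst (simulated) | 7% | 12–14% | 36–39% |
| Fisher's exact test on tissue present or absent (exact enumeration) | 4% | 29% | 77% |

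The t test rejects at its error rate because nothing it measures differs. At 40 per arm (the planned 20% dropout) the Fisher figures are about 2%, 17% and 66%.

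**Sensitivity to the assumptions.** The first model implies a large true difference. With a true 0.5 SD difference, formation of 95% versus 85%, 75% or 60%, and a correlation of 0.7 between formation and T2 (all assumed), the raw difference among measurable knees is 0.39, 0.27 or 0.12 SD. The documents support neither set of rates, so the size of the effect remains open.

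**The case against.** The strongest case on the other side is that the article leaves the matter open. The MRI outcome is listed in general terms and includes a baseline scan, taken before any regenerated cartilage exists. T2 and ΔR1 are introduced with "such as", and a test for categorical outcomes is already named. A reader might infer that these are the only MRI variables and that the trial cannot see a difference in regeneration. The text does not support that, because an imaging manual, full protocol or SAP may add fill or morphology. This part of the objection stands and limits the point to the two named measures.

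Nor does the article say that knees without tissue are excluded. A region of interest could be drawn over a poorly filled defect. No such rule is written, though, and the number obtained would not be T2 of regenerative cartilage.

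A reader might also take 22% and 3% as expected rates of absent tissue. They are symptom and function rates. The article expects microfracture to produce fibrous cartilage, and its contrast between treatments is largely one of tissue quality, for which T2 and ΔR1 are reasonable measures.

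Finally, with more absences in the control arm the selection favours control. That is conservative for the superiority hypothesis and would not create a false claim of graft benefit. This stands for the assumed direction only; an excess of lost grafts would act the other way.

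What survives is that the article does fix which tissue these two measures are taken from and how they are tested, and for a knee without that tissue the result is undefined.

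**Conclusion.** The point holds in a limited form. T2 and ΔR1, as defined, are compared only among knees with measurable repair tissue, a group selected by the treatment result. Taken alone, they cannot detect a difference in formation. On the assumed proxy of 25% to 100% of the Lysholm failure rates, the standardised difference among measurable knees shrinks by about 5% to 15%, towards the control arm, and the t test's conclusion would rarely change in that model. The true size is unknown because no absence rate is given. The point concerns one family of secondary outcomes. It is a worthwhile, inexpensive clarification, not a threat to the trial's main conclusion.

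**What to change.** Amend the T2 and ΔR1 subsections of MRI determination, the MRI item in Secondary outcome measures, and Statistical analysis:

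1. At each scheduled post-operative scan, the blinded reader records whether measurable repair tissue is present in the treated defect, and percent fill if it can be read.
2. Compare the proportion with tissue by arm, using the chi-squared or Fisher test already named.
3. Present T2 and ΔR1 as tissue quality conditional on formation.
4. Add a Mann-Whitney sensitivity analysis in which attended knees without tissue take the worst rank. For ΔR1 that is the high end, since the article says that ΔR1 falls as glycosaminoglycan content rises. For T2 the direction should be fixed beforehand.
5. State that an earlier T2 or ΔR1 is not carried forward over a later scan that shows no tissue.

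The cost is one extra field on the reading form, with no new scan or reader. The T2 and ΔR1 means become conditional descriptions. If absent tissue is as rare as the lowest assumed rate, neither the proportion nor the worst-rank test will have useful power; the gain there is that every attended, scanned knee has a reported result.
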